##### Costs related to interventions

The DBICI, a universally applicable questionnaire, has been adapted to measure the intervention costs for the two treatment groups [41, 65]. The validated DBICI has been used in RCTs with community-dwelling populations of women aged 40 years and over for non-surgical UI interventions [66] and is recommended by the International Consultation on Incontinence Research Guidelines [10, 42]. Section 1 of the DBICI documents, monthly self-reported personal incontinence expenditures (disposable and re-usable incontinence products), is used integrally. Section 2 deals with treatment expenditures and has been adapted as follows: (1) Treatment costs: rather than self-reported, treatment duration (in h) for each participant is based on statistics maintained by the research coordinators using a standardized form developed for a previous cost-effectiveness study [67]. The number of hours is multiplied by the mean hourly salary of the physiotherapists participating in the study. For the group-based PFMT, the total number of hours will be divided by the number (n = 8) of intended class participants (i.e. not actual attendance); (2) Other consultations: the frequency of visits to incontinence-related medical professionals is documented by category (general practitioners and specialists). A research assistant will phone participants at three months and six months post intervention in order to collect information. Estimated costs are based on the frequency and a mean cost per visit based on the public health system regulations for each category (Régie de l’assurance maladie du Québec). UI medication costs is excluded from the trial as those with UI medication are excluded at study entrance.

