### Objectives

The overall objective of the GROUP (Group Rehabilitation Or IndividUal Physiotherapy for Urinary Incontinence in Aging Women) trial is to determine if group-based PFMT for women aged 60 years and older with stress or mixed UI is not meaningfully less effective, sustainable, and affordable than the currently recommended individualized (one-on-one) PFMT.

The specific objectives are to compare the effectiveness of group-based PFMT vs individualized PFMT on:the % reduction in the number of UI episodes, as measured by the seven-day diary [28], immediately post intervention, and at one year post randomization (primary outcome);lower urinary track symptoms, level of distress, and quality-of-life impact, immediately post intervention and at one year post randomization. These secondary outcomes will be measured by, respectively, the seven-day bladder diary (number of urinary incontinence, number of micturition [28], the 24-h pad test (quantity of urine loss) [29], five modules of the International Consultation on Incontinence Questionnaire (ICIQ): the ICIQ-Urinary Incontinence short form (ICIQ-UI short form) [30], the ICIQ-Nocturia (ICIQ-N) [31], the ICIQ-Lower Urinary Tract Symptoms quality of life (ICIQ-LUTSquol) [32], the ICIQ-Vaginal symptoms (ICIQ-VS) [33], the ICIQ-Female Lower Urinary Tract Symptoms sex (ICIQ-FLUTSex) [34];self-efficacy, immediately post intervention and at one year post randomization, as measured by the Geriatric Self Efficacy scale [35] and the Broom Self Efficacy questionnaire Part A [36];impression of improvement and benefits, immediately post intervention and at one year post randomization as measured by the Patient Global Impression of Improvement (PGI-I) [37] and the Satisfaction and willingness to have another treatment (B&W) [17];PFM strength, function, and morphometry as measured by the digital Oxford scale [38], pelvic floor dynamometry [39], transperineal US [40] immediately post intervention and at one year post randomization.

We will also compare the direct costs of group-based PFMT and individualized PFMT using the adapted Dowell–Bryant Incontinence Cost Index (DBICI) [41] immediately post intervention and at one year post randomization.

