#### Individualized PFMT

The only specificity of this treatment group is that women participate in one-on-one, 1-h sessions with intra-vaginal electomyography (EMG) biofeedback under the supervision of an experienced physiotherapist. This treatment approach is in line with clinical practice in Canada [53].

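### The stated treatment-cost rule has no item for the EMG biofeedback used only in the individual arm, so taken alone it understates that arm's direct cost by an unknown amount per woman

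*Protocol article*

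**What the plan says.** The Objectives section of the protocol article promises a cost comparison: "We will also compare the direct costs of group-based PFMT and individualized PFMT", using the adapted DBICI cost questionnaire. The section Costs related to interventions describes what that questionnaire collects.

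- Section 1 covers the woman's own spending: "monthly self-reported personal incontinence expenditures (disposable and re-usable incontinence products), is used integrally".
- Section 2, first item, is treatment cost. The input is time: "treatment duration (in h) for each participant is based on statistics maintained by the research coordinators". The price is salary: "The number of hours is multiplied by the mean hourly salary of the physiotherapists" in the study. For classes, "For the group-based PFMT, the total number of hours will be divided by the number (n = 8) of intended class participants", whatever the attendance.
- Section 2, second item, is other consultations: "the frequency of visits to incontinence-related medical professionals is documented by category (general practitioners and specialists"), priced from public tariffs.
- Incontinence medication is left out, and a reason is given.

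The section Individualized PFMT describes that arm as "one-on-one, 1-h sessions with intra-vaginal electomyography (EMG) biofeedback". The notes to Table 2 tie the biofeedback probe to the individual group and say that its use depends on the week. The section Group-based PFMT describes classes of eight (minimum six if recruitment is slow) with up to three optional 20-minute private sessions, and mentions no biofeedback.

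The Economic analysis section builds an incremental cost-effectiveness ratio on these costs. Its one sensitivity analysis restricts each participant's cost to the interquartile range.

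**The concern.** By the article's own description the arms differ in two treatment resources: physiotherapist time per woman, and biofeedback. The rule prices the first and has no place for the second. A probe and device used in a session are direct costs of that session on the same footing as the physiotherapist's salary, and the article declares no costing perspective that would include one and exclude the other. Followed as written, the rule enters biofeedback at zero for every woman.

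The article ties a change in practice to group treatment being both non-inferior and more cost-effective. If group treatment turns out somewhat less effective but within the 10% margin, decision-makers will weigh the saving against the effect given up. That ratio would then rest on a saving that leaves out one arm-specific cost.

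**Working it through.** The article states no salary, equipment price or expected cost difference, so there is no figure to reproduce. The check is to apply the stated rule symbolically.

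**Inputs from the protocol article**
- 12 weekly sessions of 1 h in both arms (Interventions; PFMT sessions).
- Class divisor of 8 (Costs related to interventions).
- Optional private sessions in the group arm: up to 3 × 20 min = 1 h (Group-based PFMT).
- Minimum class size of 6 (Group-based PFMT).

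**Inputs not in the article**
- W, the mean hourly salary.
- B, the biofeedback cost per woman in the individual arm (probe, consumables and device share).

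**Step 1. The rule as written, with full attendance**
- Individual arm: 12 × 1 × W = 12W.
- Group arm, classes only: (12 / 8) × W = 1.5W. Difference: 12W − 1.5W = 10.5W.
- Group arm with all private sessions used and charged in full to the woman: 1.5W + 1W = 2.5W. Difference: 12W − 2.5W = 9.5W.

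**Step 2. Biofeedback added to the individual arm**
- Difference: 10.5W + B, or 9.5W + B with private sessions.
- The shortfall is exactly B per woman. As a share of the corrected difference it is B / (10.5W + B).

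**Step 3. Illustration only; every value of W and B is assumed**

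| W | B | As written (10.5W) | With B | Shortfall |
|---|---|---|---|---|
| 60 | 25 | 630 | 655 | 3.8% |
| 40 | 75 | 420 | 495 | 15.2% |
| 30 | 300 | 315 | 615 | 48.8% |

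A span from 3.8% to 48.8% shows that the article does not determine the size.

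**Step 4. What pushes the other way in the same rule**
- If a class has six women, class time per woman is 12 / 6 = 2.0 h, not 1.5 h. Dividing by 8 undercounts the group arm by 0.5W.
- The text can also be read as dividing all group-arm hours by 8, private sessions included. A woman who used the full hour would be charged 1/8 h for it, a further undercount of 0.875W.
- Together these reach at most 0.5W + 0.875W = 1.375W. At an assumed W = 40 that is 20 + 35 = 55.
- The net error in the difference therefore lies between B (classes of eight, private time charged in full) and B − 1.375W (classes of six, full private use, all hours divided by 8). Its sign depends on W, B, class sizes and private-session use.

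**Step 5. Does the planned sensitivity analysis help?** Limiting costs to the interquartile range works on the costs as computed. It cannot restore an item that is zero for every woman.

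**The case against.** The strongest reply is that the text never says staff time is the *only* treatment cost. It explains how part of an existing questionnaire was adapted, refers to a standardized form from a previous study that is not shown, and is a journal article, which may leave a unit-cost list to the full protocol. This has some force, and an equipment line may exist elsewhere. But the article does more than stay silent: it lists the two items of Section 2 and gives the formula for the first. Where it drops a cost, medication, it says so and why. Read as it stands, the rule gives biofeedback no cost.

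Second, the omission makes the individual arm look cheaper, so on its own it makes a saving from group treatment harder to show and cannot create a false one. That stands. It limits the harm, but it does not make the size of the difference or ratio right.

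Third, probe use varies by week, and devices may already be owned or shared with other patients. That also stands. It bears on how large B is, not on which arm it belongs to.

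A reader might infer that the cost-effectiveness result is shown to be biased against group treatment by a material amount. The article does not support this. No unit cost is given, and the division by eight works in the opposite direction, so neither the size nor the net direction for the whole cost rule is established.

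**Conclusion.** The point holds in a limited form. The stated treatment-cost rule omits a direct cost that arises in one arm only. Taken alone, the omission understates the individual-arm cost, the saving from group treatment and the numerator of the ratio by B per woman. This rests on reading the two-item list as complete and on biofeedback being confined to the individual arm, as the article describes.

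B cannot be derived from the article, and any percentage is illustrative. The omission is conservative for a claim that group treatment is cheaper, is partly offset by the divisor of eight where groups are smaller, and has no bearing on the primary non-inferiority test. It is a minor point, worth correcting because cost-effectiveness is one of the two results on which the article rests a change in practice.

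**What to change.** In the first item of DBICI Section 2, define treatment cost as staff time plus arm-specific equipment and consumables. For the individual arm, add a per-woman probe cost and an amortised share of the biofeedback device, taken from the centres' purchase records and adjusted for actual use and for use outside the trial. Report the cost difference and the cost-effectiveness ratio with and without this item, over a range of B. If equipment is left out on purpose, say so, give the reason, and still show the range.

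The cost is small: two unit costs and an extra line in the cost table. No change to the design or the primary analysis is needed. The downside is that an amortisation period has to be assumed, so it should be varied in the sensitivity analysis.

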#### Group-based PFMT

The only specificity for this treatment group is that women participate in groups of eight in a weekly 1-h session, under the supervision of an experienced physiotherapist. They are also offered up to three optional private (20 min) sessions with the physiotherapist leading their group (either before or after a group session) to ensure understanding and correct performance of a PFM contraction – as confirmed by vaginal digital palpation [17]. This treatment approach is consistent with Bo’s PFM exercise class [54] and our more recent pilot cohort studies indicating it is both feasible and effective intervention for UI in aging women [18, 55]. In case of slow recruitment, we have established a minimum group size of six participants in order to avoid delays for those assigned to group physiotherapy.

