To err on the conservative side, we relied on the “standard” 95% CI, which corresponds to a stringent one-tailed type I error rate of α = 0.025 (2α = 1–0.95 = 0.05). Similar to other recent non-Inferiority trials (e.g. [70, 71]) and CONSORT guidelines [68], for the purpose of sample size calculation, we assume that the true difference between the mean reductions (%) achieved by the two interventions will be zero (i.e. that they are equally effective). Note that this assumption of equivalence of the two interventions being compared in our trial is consistent with both (a) clinical expectations and (b) (limited) published evidence concerning young and middle-aged UI women [72–74]. Finally, both published trials, which evaluated similar interventions in older women, reported within-group standard deviations (SD) of the individual % reduction scores of about 27% [44, 75]. Accordingly, we assumed SD = 27% in our calculations.

Under the above assumptions, we estimated the sample size needed to ensure high (90%) power to demonstrate the non-inferiority of the group-based intervention (assuming, as mentioned above, that the true difference is 0%). Thus, we calculated N, for which the probability that the upper boundary of the two-tailed 95% CI for the difference in the mean relative reduction (Individual – Group) excludes the “upper threshold of non-inferiority” (10% difference), will reach at least 90%. The sample size calculations were performed using the program in the PASS software package, designed specifically for power/sample size estimation for non-inferiority trials [76]. Under the assumptions outlined above, we will need 155 participants per group, for a total of 310 individuals. We also need to account for possible losses to follow-up, as we expect a 15% attrition rate by the end of the one year, based on both our pilot data and similar published trials [16, 17, 22, 51]. Thus, we will recruit an additional 54 participants per group, increasing the total number of participants to 364 (364*(1–0.15) = 310).

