To ensure evaluation and treatment adherence, we used the following strategies: (1) individual consultations using vaginal digital palpation ensure that participants can perform a PFM contraction correctly (the physiotherapist is available before and after individual and group treatment sessions to provide tips and answer questions regarding the weekly treatment and home exercise program); (2) an exercise diary is given to each participant to bring home and is verified by the physiotherapist each week throughout the treatment; (3) the home exercise program comprises a short and simple daily PFM exercise program to facilitate exercise practice; (4) women in both groups are reminded of their appointments (evaluation and treatments) by a research assistant. They are scheduled at participants’ convenience; (5) follow-up contact calls are made at three and six months post intervention to maintain contact. Evaluators solicit information from participants on their intention to change address or telephone number and on the frequency of visits to incontinence-related medical professionals. They also verify if medications have been prescribed, surgery conducted, and if there are any other health problems likely to influence UI. Finally, they monitor their continued adherence to PFMT; and (6) participants are reimbursed for their travel and parking expenses related to participation in the study.

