#### Economic analysis

Mean, median, and interquartile (semi-IQ) will be used to describe the costs for the two groups. Cost-effectiveness analysis will be performed on the main outcome: reduction in number of leakages (%) one year after randomization and expressed as a ratio of incremental costs and percentage of leakages. In order to verify the robustness of the economic analysis, a sensitivity analysis will be conducted on the hypothesis that the costs for each participant should be between the 25th and 75th percentiles of the cost distribution.

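### The planned cost-effectiveness ratio has an expected denominator of zero; the fixed class divisor of eight and the entry-only reason for omitting medication costs are smaller faults in the same analysis

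*Protocol article*

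**What the plan says.** All places are in the protocol article.

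- **Class hours** (Costs related to interventions): treatment cost is hours times the mean physiotherapist salary. For the group arm, "the total number of hours will be divided by the number (n = 8) of intended class participants (i.e. not actual attendance".
- **Class size** (Group-based PFMT): classes are planned for eight, but if recruitment is slow "we have established a minimum group size of six participants in order to avoid delays". The same section adds for this arm: "They are also offered up to three optional private (20 min) sessions with the physiotherapist leading their group".
- **Medication** (Costs related to interventions): "UI medication costs is excluded from the trial as those with UI medication are excluded at study entrance". Table 1 nevertheless admits users who are comfortable stopping, and at the three- and six-month follow-up calls (Adherence) the evaluators ask about new treatment: "They also verify if medications have been prescribed, surgery conducted".
- **Summary measure** (Economic analysis): the result on the one-year primary outcome is "expressed as a ratio of incremental costs and percentage of leakages".
- **Effect assumed in planning** (Sample size calculation): "we assume that the true difference between the mean reductions (%) achieved by the two interventions will be zero". The article describes this as in line with clinical expectations and with limited published evidence.
- **Robustness check** (Economic analysis): the one sensitivity analysis stated rests on the hypothesis that "the costs for each participant should be between the 25th and 75th percentiles of the cost distribution".

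**The concern.** A ratio of incremental cost to incremental effect is informative only when the effect difference is clearly away from zero. This trial is planned on the expectation that it is zero, so the better the trial confirms its own hypothesis, the less the ratio says. The meaning also flips with the sign. If group treatment is cheaper, a negative ratio means cheaper and better, while a positive one means a saving bought with some loss of effect.

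Two costing rules add smaller problems. Ignoring attendance when sharing out class hours is reasonable; ignoring the size at which the class was formed is not. And a criterion applied at entry says nothing about medication started or resumed after randomization, which the trial asks about.

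The Abstract, Background and Discussion pair non-inferiority with better cost-effectiveness when they argue for group treatment, so the economic result carries part of the intended conclusion.

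**Working it through.** **Inputs.** SD 27 points, margin 10, true difference 0, one-sided alpha 0.025, power 90%, 155 per arm (Sample size calculation). Twelve weekly sessions of 1 h in both arms (Interventions; PFMT sessions). Classes of eight, minimum six, and up to 3 × 20 min = 1 h of private time per woman (Group-based PFMT). No salary is given, so costs are in physiotherapist hours.

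**The plan's own figure.** The normal approximation, 2 × (1.960 + 1.282)² × 27² / 10², gives 154 per arm. The noncentral t gives power 0.8997 at 154 and 0.9015 at 155. The stated 155 is reproduced.

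**Denominator of the ratio** (group minus individual, in points):

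- SE = 27 × √(2/155) = 3.07; 1.96 × 3.07 = 6.0. The estimate therefore ranges over about −6.0 to +6.0 around 0.
- The probability of either sign is 50%. The probability of lying within 1 point of zero is about 26%.
- For a fixed cost difference of −10 units, the outer 2.5% on each side is reached where the denominator is within 0.0627 SE of zero: 10 / (0.0627 × 3.07) ≈ 52. The central 95% of ratios is about −52 to +52 per point. One million simulated draws with a saving of 10.5 h gave −54 to +55.
- The 95% Fieller interval is unbounded whenever the estimate lies within 1.96 SE of zero: 95% of trials at a true difference of 0, 87% at 2.5 points, 63% at 5 points.

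These figures hold cost fixed, so they isolate the effect of the denominator.

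**Class divisor, no private sessions:**

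| Women in class | Hours per woman, actual | Hours charged | Saving vs 12 h, actual | Saving under the rule |
|---|---|---|---|---|
| 8 | 12/8 = 1.50 | 1.50 | 10.50 | 10.50 |
| 7 | 12/7 = 1.71 | 1.50 | 10.29 | 10.50 |
| 6 | 12/6 = 2.00 | 1.50 | 10.00 | 10.50 |

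A class of six is charged 25% too little (0.5/2.0), but the saving is overstated by 0.5/10.0 = 5%, and only if every class has six. Some shortfall is built in: 364/2 = 182 per arm and 182/8 = 22.75, so not every class can have exactly eight.

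**Private sessions, all three used, class of six.** Actual hours are 2.0 + 1.0 = 3.0 per woman, a saving of 9.0 h.

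- Private time charged to the woman, class time divided by eight: 1.5 + 1.0 = 2.5 h, saving 9.5 h, overstated by 0.5/9.0 = 5.6%.
- Her class and private hours both divided by eight: 13/8 = 1.625 h, saving 10.375 h, overstated by 1.375/9.0 = 15%.

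The text does not settle which reading applies.

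**Separating the two issues.** Replacing 10.5 h by 10.0 h changes any given ratio by about 5%. The instability comes from the denominator, not from the costing rules.

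**Percentile check.** By definition about half of the values lie outside the 25th to 75th percentiles. Whether these are dropped or limited to the range, the high-cost tail, on which a mean cost depends, is removed or flattened. Neither class size nor the denominator is varied.

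**The case against.** A fair defence has several parts.

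- Zero is a sample-size assumption, not a forecast. This helps only a little: the article also calls it the clinical expectation, and at a true difference of 5 points the Fieller interval is still unbounded in 63% of trials.
- The ratio is not the only output. Economic analysis describes costs by arm, and Objectives lists a direct-cost comparison. With non-inferiority shown, cost could be judged from these. This stands and limits the damage.
- Net benefit, bootstrap intervals and cost-effectiveness planes may be left to a fuller document. Their absence is indeed no finding; the point is that the summary form the article does fix is a poor one for this design.
- Six is a contingency, and costing at the intended size is defensible if the question is routine delivery. That supports eight as a scenario, not as the cost of classes actually run with fewer women.
- Home PFMT program asks all women to refrain from other treatment, which partly supports leaving medication out. It is a request, and the follow-up calls still check.
- Secondary analyses are called exploratory, and the rationale for the non-inferiority design ties a change of practice to non-inferiority alone. The economic result is thus not uniformly presented as decisive.

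A reader might infer that the costing rules as a whole tilt the result toward the group arm. The documents do not support that. Omitting medication favours the group arm only if that arm uses more of it, and nothing says so. EMG biofeedback, specified for the individual arm (Individualized PFMT), has no equipment charge in the stated treatment-cost rule, which works against the group arm. The article does not say that surgery costs are left out, and it does not clearly say that private sessions are divided by eight.

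**Conclusion.** The point holds in three parts of unequal weight.

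1. **The ratio (main point).** Under the plan's own assumption its denominator is 0 with SE 3.07 points, so its sign and size are mostly noise. The stated sensitivity analysis does not address this. The result rests on SD 27, 155 per arm and a fixed cost difference.
2. **The divisor.** Eight conflicts with the permitted minimum of six and, in classes below eight, can only lower the group arm's cost. The class-hour saving is overstated by 0 to about 5% (10.5 against 10.0 h). The share of smaller classes is not given. The group arm uses less therapist time in every scenario examined, including the least favourable reading of the private sessions.
3. **Medication.** The stated reason covers entry only, so costs are incomplete. No direction or size can be derived from the article.

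A claim of systematic bias in favour of group treatment would go beyond this. The whole is worth correcting, but it does not touch the primary non-inferiority analysis.

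**What to change.** - Make the mean cost difference and the incremental net benefit (willingness to pay per point × effect difference − cost difference), over a range of willingness-to-pay values and with bootstrap CIs, the main economic summary in place of the ratio. Net benefit has no denominator and stays well defined when the effect difference is zero.
- Divide class hours by the number of women allocated to that class, still not by attendance, and keep eight as a sensitivity analysis.
- State that private-session time is charged undivided to the woman who used it.
- Cost the UI medication recorded after randomization in both arms, and say whether recorded surgery is costed.
- Replace the restriction to the 25th to 75th percentiles by varying unit costs and class size.

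The cost is mainly a change of analysis wording and use of data already recorded. Unit costs for drugs must be added, and the group arm's cost advantage may become slightly smaller.

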### Recruitment

Women are being recruited from community advertisements, newspaper ads, the Research Center of the Institut Universitaire de Gériatrie de Montréal’s bank of participants, gynecology and urology clinics within the metropolis of the two study centers. In Montreal, these include the gynecology clinic at the Maisonneuve-Rosemont Hospital, and the CHUM gynecology clinics, the CLSC Lucille Teasdale, the CSSS Jeanne Mance. In Sherbrooke, this includes the urology and gynecology clinics at the Centre Hospitalier Universitaire de Sherbrooke. A poster explaining the research project is being displayed at each clinic. Interested candidates are invited to call the research coordinator.

Determination of eligibility is achieved in two steps: (1) telephone eligibility evaluation with a research assistant; and (2) on-site eligibility evaluation with the evaluator. Participant eligibility criteria are described in Table 1. These criteria ensure recruitment of a homogeneous sample of community-based older women with stress/mixed urinary incontinence signs and symptoms. Women excluded from the study are referred back to their healthcare provider to receive standard incontinence care.

**Table 1 Tab1:** Inclusion and exclusion criteria

Inclusion criteria	
- Aged 60 years and over - Have stress or mixed urinary symptoms at least three times a week persisting for three months or more	
- Able to have a gynecological examination	
Exclusion criteria	
- Have a BMI ≥ 35; - Reduced mobility (not able to get around without the aid of a cane, crutches, or a walker) - Suffer from untreated chronic constipation - Experience important organ prolapse (POPQ > 2) - Received physiotherapy treatment for urinary incontinence in the past year - Have a surgery for incontinence or organ prolapse in the past year - Currently taking any medication for urinary incontinence (eligible if comfortable stopping the medication) or medications affecting skeletal muscles - Experiencing any leakage of stool or mucus - Have an active urinary or vaginal infection in last three months - Recent change in hormonal replacement - Any co-morbidities or risk factors interfering with the study (e.g. respiratory, cardiovascular, or memory problems, active cancer, diabetes, etc.)	

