### Home PFMT program

Women in both groups are expected to perform PFM strengthening, endurance, and coordination exercises at home, five days a week, for the duration of the treatment [18, 22, 51, 55]. To support progression in the treatment, the home exercise program parallels the three phases in the treatment protocol with the gradual addition of increasingly difficult exercises every four weeks. To standardize home PFM exercises, each participant is given a PFM exercise diary describing the home PFMT exercises, in which they can record their adherence to the home program. Finally, all participants are asked to refrain from seeking other forms of treatment (such as medication or surgery) during the study.

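### UI medication costs are excluded for a reason that holds only at entry, so drugs started or restarted during the year are priced at zero and the cost of treatment failure is only partly captured

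*Protocol article*

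**What the plan says.** All places are in the protocol article.

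- **Costs related to interventions.** Medication is removed from the costing with one stated reason: "UI medication costs is excluded from the trial as those with UI medication are excluded at study entrance". Two items that follow the programme are costed. The first is DBICI Section 1, where "monthly self-reported personal incontinence expenditures (disposable and re-usable incontinence products), is used integrally". The second is other consultations, where "the frequency of visits to incontinence-related medical professionals is documented by category (general practitioners and specialists"; these are multiplied by a mean public-tariff cost per visit. Programme cost is therapist hours times mean salary, divided by eight for the group arm.
- **Recruitment, Table 1.** The exclusion criterion reads "Currently taking any medication for urinary incontinence (eligible if comfortable stopping the medication) or medications affecting skeletal muscles".
- **Home PFMT program.** "all participants are asked to refrain from seeking other forms of treatment (such as medication or surgery) during the study".
- **Adherence.** "follow-up contact calls are made at three and six months post intervention to maintain contact". On what evaluators ask: "They also verify if medications have been prescribed, surgery conducted, and if there are any other health problems likely to influence UI".
- **Objectives and Economic analysis.** Direct costs are compared after the intervention and at one year. The cost-effectiveness ratio uses percentage reduction in leakages one year after randomization.

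**The concern.** An entry criterion fixes medication status at baseline. It says nothing about the following year, and the costing covers that year. The protocol expects that some women may turn to other treatment, because it asks about prescriptions and surgery in the follow-up calls. Drugs begun after training has not worked well enough are a direct cost of treatment failure, and the rule enters them as zero.

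The effect side of the ratio has no matching rule. Under Data analysis, the main analysis set is the women who complete the one-year assessment, and the article does not remove those who took a drug meanwhile. Any leakage reduction obtained with a drug is credited to the arm while the drug itself costs nothing.

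What is at stake is the claim that group training is more cost-effective. The Discussion pairs that claim with clinical effectiveness as grounds for wider use of group training.

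**Working it through.** The plan gives no figure on this point, so there is none to reproduce. The check sets the passages side by side and then writes out the error the rule produces.

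**1. Does the stated reason support the exclusion?** It would need two things to be true.
- *No user enters the trial.* Table 1 is not absolute: current users are eligible if comfortable stopping. Such women could restart.
- *No one starts during the year.* Home PFMT program makes this a request to participants, and Adherence has evaluators verify whether it happened.

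Neither is secured by the text.

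**2. Which consequences of persistent incontinence are priced?**
- Pads and products: recorded and priced.
- General practitioner and specialist visits: recorded and priced.
- Medication: prescriptions are asked about; cost excluded by express rule.
- Surgery: asked about; no cost item is listed in Costs related to interventions or Economic analysis.

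The plan would thus price the visit at which a drug is prescribed but not the drug.

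**3. Size of the error.** Let pG and pI be the proportions in the group and individual arms who start or restart UI medication after randomization, and c the mean cost per user within the year, taken as equal in both arms. For the cost difference, group minus individual:

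true difference = planned difference + (pG − pI) × c

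- Equal uptake: (0) × c = 0, no error.
- Assumed uptake difference of 2 points and c = 100 currency units: 0.02 × 100 = 2 units per participant.
- Assumed uptake difference of 10 points and c = 5000: 0.10 × 5000 = 500 units per participant.

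With the sign of (pG − pI) reversed, the error favours the individual arm by the same amount.

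**4. Scale against the programme saving, for illustration only.** Therapist time per woman is 12 h individually and 12/8 = 1.5 h in a group, a saving of 12 − 1.5 = 10.5 h. If every group-arm woman used all three optional 20-minute private sessions and these were charged in full, the group figure rises by 3 × 20 min = 1 h and the saving falls to 9.5 h. Assume a drug course costing the equivalent of 7.5 to 25 therapist hours and 10 points more users in the group arm. The omitted cost is then 0.10 × 7.5 = 0.75 h to 0.10 × 25 = 2.5 h. That is 7% to 24% of 10.5 h, or 8% to 26% of 9.5 h. Both the uptake difference and the prices are assumptions, and the range starts at 0% for equal uptake.

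**5. Period covered by the calls.** If training starts at randomization, the last call falls about 12 weeks plus six months later, roughly 2.8 + 6 = 8.8 months. About 12 − 8.8 = 3.2 months of the costing year then remain. The article places a cost assessment at one year but does not say whether the medication question is repeated there.

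**The case against.** The strongest reply is that a restricted cost perspective is legitimate. The objective reads "We will also compare the direct costs of group-based PFMT and individualized PFMT using the adapted Dowell–Bryant Incontinence Cost Index (DBICI", and the costing section is titled as costs of the interventions. Women are asked not to seek medication or surgery, so uptake may be low. The design also assumes equal effectiveness, and if uptake is then equal the omission cancels. What stands is that uptake may be small and the bias may be nil. What does not stand is the perspective argument as a defence of this rule: the plan already goes beyond programme cost by counting products and medical visits, and the reason it gives for leaving drugs out is the entry criterion, not a chosen perspective.

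Three stronger readings are tempting and are not supported.

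- *A reader might infer that the cost of treatment failure never enters the comparison.* Products and consultations are counted, and both can be expected to rise when treatment fails.
- *A reader might infer that surgery and further physiotherapy are costed at zero by rule.* Only medication is excluded expressly. The article condenses a fuller protocol, its silence on surgery is not a rule, and the follow-up check it describes does not mention physiotherapy.
- *A reader might infer that the result is biased toward the group arm.* That holds only if the group arm has more uptake. The rationale for the non-inferiority design names possible long-term benefit from group delivery, which would turn the bias the other way.

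It is also fair to say that the follow-up check sits under Adherence, speaks of medications generally, and is not described as recording drug name or duration. It cannot be priced as it stands without added detail.

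**Conclusion.** The concern holds in a limited form. The medication exclusion rests on a reason that does not cover the period being costed, and it conflicts with what the protocol itself admits at entry and checks during follow-up. The cost of treatment failure is partly captured: products and medical visits are in, drugs are out by rule, and surgery has no listed cost although it is asked about.

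The resulting error in the cost difference is (pG − pI) × c. It favours whichever arm has more uptake and is zero if uptake is equal. The documents supply neither uptake nor unit prices, so its size is unknown, and the figures in the working only show how it scales. The conclusion on direction assumes a similar cost per user in both arms. The point concerns the economic comparison only; the sample size and the primary non-inferiority test are untouched.

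**What to change.** - In Costs related to interventions, delete the sentence excluding medication costs.
- Cost UI medication started or restarted after randomization, using the existing follow-up checks with drug and duration recorded, at public-plan unit prices.
- Do the same for UI surgery, if the full protocol does not already do so.
- Ask the same question at the existing one-year assessment, unless it is already asked there, so that the whole costing year is covered.

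The cost is a wording change, a unit-price table, and slightly more data collection and costing work. With 353 of 364 women recruited at the time of the article, some will be past their calls, and for them the detail may have to be obtained retrospectively at the one-year visit, with some recall error. The group-arm saving may come out smaller.
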